### Patient and public involvement

Patients and public were not involved in developing the research questions nor the study design. Moreover, they will not participate in the recruitment exercise or the conduct of the study. Results of the study will be disseminated to participants and their families via telephone and patient organization platforms.

### Outcome measurement

The primary outcome will be the number of eggs obtained, and the secondary outcome will include the 2PN number, cleavage number, grade I embryo number, implantation rate, abortion rate, persistent pregnancy rate, trigger day ≥ 14 mm follicles, Gn days, and Gn.

### Data analysis

All data are reported as mean ± standard deviation (SD). Patients with low adherence will not be included in the final analysis, but will be included in the intention-to-treat analysis. Two sets of analyses will also be performed for non-adherence and missing outcomes. The full analysis set (FAS) will include all patients who are randomized and will proceed according to the intention-to-treat principle. The protocol-compliant set will include all patients in the FAS who completed follow-up and did not experience a serious protocol violation.

For baseline comparisons, differences in means of continuous data between the placebo and intervention groups will be evaluated using independent Student’s *t* tests or Mann-Whitney *U* tests, depending on whether the data are normally distributed, and frequencies will be compared using chi-square tests. For longitudinal data with baseline, we will evaluate mean differences between and within groups using repeated measures analysis of covariance (ANCOVA). All tests will be two-tailed and ratios between the two groups will be compared using Fisher’s exact rate method with a significance level defined as a value < 0.05.

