### Trial design

This is a prospective, randomized, placebo-controlled, double-blind, superiority trial assigned in a 1:1 ratio. The study institutions were the Genetic and Reproductive Center of Traditional Chinese and Western Medicine, Affiliated Hospital of Shandong University of Traditional Chinese Medicine, the Second Affiliated Hospital of Shandong University of Traditional Chinese Medicine, and Jinan Central Hospital. The project leader regularly coordinates and communicates with each unit to understand the progress of the project and ensure the smooth progress of the project and the guarantee of quality. In order to ensure that there are enough participants, we will take measures such as providing free basic examinations, free drugs, and car allowance to better attract participants to join.

The inclusion criteria for this study will be patients aged between 35 and 42 years old, with insufficient ovarian reserve parameters (The POSEIDON criteria AFC < 5, AMH < 1.1 ng/mL) [18], and poor ovarian response (that is, the number of oocytes obtained after standard ovarian stimulation is less than 3). Patients should meet the diagnostic criteria of western medicine infertility, that is, women living without contraception for at least 12 months who are not pregnant are infertile [19].

The exclusion criteria are women with BMI ≥ 25 kg/m^2^; women who suffer from genetic diseases that are not suitable for childbearing as stipulated in the Maternal and Child Health Care Law; women with severe endometriosis, adenomyosis, and immune infertility; with untreated hydrosalpinx; with congenital or acquired abnormal development of the uterus and severe deformities of other reproductive organs; women with a history of endocrine dysfunction such as reproductive system tumor, thyroid dysfunction, and hyperprolactinemia; women receiving ovarian stimulation therapy or OCP in recent 3 months; women with a previous history of gynecological surgery such as the ovary; and all other contraindications of assisted reproductive technology.

The discontinuation criteria will be women who have adverse reactions such as nausea and obesity occurring during medication, women with no dominant follicular growth, early follicular ovulation, and no egg acquisition during ovarian stimulation. Three days after egg harvesting, the embryo was not formed.

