### Case registration and allocation

The clinicians being involved in the study will record the basic AFC and AMH values of the patients after obtaining informed consent from the participants. Upon meeting the inclusion criteria, the patients will be randomly distributed in groups with the order of registration, and the clinicians are responsible for recruiting patients in sequence and will use case questionnaires to record their identity, age, and other basic information.

The clinicians will give medication to participants within 3 days after screening. Data will be recorded on drug distribution and use, and timely reports provided to the clinicians on the drug dose and patients’ discomfort during the process.

This study will include 120 patients who will be recruited and randomly divided into two groups using the R language version 3.5.1: the elderly test group and the elderly control group. Sixty, patients will be treated with Guilu Xian and 60 with the placebo. The elderly and the experimental group will be treated with an antagonist, and the tortoise deer fairy and placebo will be administered from the third day of menstruation before IVF.

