### Randomization and blinding

After signing the informed consent form, volunteers participating in the trial were randomly assigned to one of the two trial groups in a 1:1 ratio using stratified zone group randomization, and random numbers were generated using R software version 3.5.1. A strictly confidential list of randomization numbers will be maintained by the dosing center staff. Randomization will be stratified by trial center in different regions. The active drug (Guilu Xian) and placebo will be manufactured with similar appearance and smell. The clinicians and patients will be blinded to the drug allocation until the end of the study. If there are multiple adverse reactions in the trial, we will take emergency unblinding measures to find the cause of adverse events. To achieve high precision, the trial will follow the Consolidated Standards of Reporting Trials (CONSORT) 2010 statement [20] and the updated guidelines for reporting parallel-group randomized trials of the traditional Chinese medicine CONSORT [21].

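### The Data analysis section assigns no efficacy analysis to the primary outcome, and no stated analysis uses the stratification factor or the recorded baseline AFC, AMH and age; the cost is precision, not bias

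*Protocol article*

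**What the plan says.** All references are to the protocol article.

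- **Outcome measurement:** "The primary outcome will be the number of eggs obtained". The secondary outcomes include other once-measured counts: 2PN, cleavage, grade I embryos, and follicles of at least 14 mm on trigger day.
- **Data analysis, first method:** "For baseline comparisons, differences in means of continuous data between the placebo and intervention groups will be evaluated using independent Student’s" t tests, or by Mann-Whitney tests if the data are not normal, with chi-square tests for frequencies.
- **Data analysis, second method:** "For longitudinal data with baseline, we will evaluate mean differences between and within groups using repeated measures analysis of covariance (ANCOVA").
- **Data analysis, third method:** "ratios between the two groups will be compared using Fisher’s exact rate method".
- **Data analysis, population:** the full analysis set holds all randomised women and follows the intention-to-treat principle.
- **Randomization and blinding:** "Randomization will be stratified by trial center in different regions". Three hospitals take part.
- **Case registration and allocation:** clinicians "record the basic AFC and AMH values of the patients after obtaining informed consent", before allocation. Age goes on the case questionnaire.
- **Trial design:** entry is limited to ages 35 to 42 and "AFC < 5, AMH < 1.1 ng/mL". Failure to obtain eggs is among the discontinuation criteria.
- **Estimation of the sample size:** a two-sided Z test with combined variance, comparing mean egg numbers of 11 and 9. It is named only for that calculation.

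**The concern.** A reader who wants to know how the primary result will be obtained does not find it in the section meant to say so. Egg number has no baseline value and is not repeated, so the repeated-measures method has nothing to work on. It is not a ratio, so Fisher's test does not apply. It is not a baseline characteristic, so the two-sample tests, as scoped, do not apply either. The same gap affects the secondary counts.

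The article also fixes a stratified design and then states no analysis that uses the strata. Balancing arms within centre removes between-centre variation from the treatment comparison. An analysis that leaves centre out keeps that variation in its standard error, which is then too large. AFC, AMH and age are the trial's own entry markers and are on record before treatment, yet no stated analysis uses them. What is at stake is the clarity of the primary analysis and some avoidable loss of precision in a trial of 120 women.

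**Working it through.** The documents give no figure for this point to reproduce, so the check has three parts.

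**1. Match each stated method to the primary outcome.**

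| Method in Data analysis | Stated scope | Does egg number fall in it? |
|---|---|---|
| t test or Mann-Whitney; chi-square | Baseline comparisons | No, it is measured after treatment |
| Repeated-measures ANCOVA | Longitudinal data with a baseline | No, there is one value and no baseline |
| Fisher's exact test | Ratios | No, it is a count |

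No row covers it. Centre, AFC, AMH and age appear in no row.

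**2. Effect of leaving out centre after stratified 1:1 randomisation.** Let ρ be the share of egg-count variance explained by centre (assumed; the article gives none). The unadjusted test uses the total variance, but the true variance of the treatment difference is only (1 − ρ) of what the test assumes. The real type I error at a nominal two-sided 5% is therefore

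2 × [1 − Φ(1.96 / √(1 − ρ))]

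| ρ | 1.96 / √(1 − ρ) | Type I error |
|---|---|---|
| 0 | 1.960 | 5.0% |
| 0.05 | 2.011 | 4.4% |
| 0.10 | 2.066 | 3.9% |
| 0.20 | 2.191 | 2.8% |

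A simulation agrees. It used 120 women, three centres of 40, blocks of 4, rounded counts, 3,000 null trials per setting, and an assumed SD of 3.05. The unadjusted t test rejected in 4.8% to 5.2% of trials for ρ of 0.02 to 0.05, in 3.5% to 3.7% for ρ = 0.10, and in 2.7% for ρ = 0.20. Models with centre, with or without a covariate, stayed near 5% (4.5% to 5.8%).

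The SD of 3.05 is not in the article. It is the value that gives the planned 49 per group for a difference of 2 eggs at 90% power: 2 × [3.05 × (1.960 + 1.282) / 2]² = 48.9, rounded up to 49. It only sets the scale of the simulation.

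**3. Gain from baseline variables.** Let R² be the share of variance that AFC, AMH and age explain (assumed). Adjustment multiplies the standard error by √(1 − R²), which is worth a sample 1 / (1 − R²) times as large.

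| R² | √(1 − R²) | Cut in standard error | 1 / (1 − R²) |
|---|---|---|---|
| 0.05 | 0.975 | 2.5% | 1.05 |
| 0.10 | 0.949 | 5.1% | 1.11 |
| 0.20 | 0.894 | 10.6% | 1.25 |
| 0.30 | 0.837 | 16.3% | 1.43 |

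In the same simulation with a true difference of 1.5 eggs (2,000 trials per setting), power was 75% to 79% with the unadjusted t test, 76% to 86% with centre, and 80% to 96% with centre plus a covariate of R² 0.1 or 0.3. These ranges run over ρ from 0.02 to 0.20.

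**The case against.** The strongest reply is that this is loose drafting in a condensed article. A t or Mann-Whitney test is usable for one count per woman in two randomised arms, and only the words limiting it to baseline stand in the way. The sample-size section plans on a difference in means, so a two-sample comparison was probably intended. Covariate lists are often left to an analysis plan, which is not shown, and the article never says that centre or baseline values will be left out.

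Much of this stands. A rescoped two-sample test would be valid, and the AFC, AMH and age part is the weaker half. What does not fall away is that the article has an analysis section, scopes its methods, and misses the primary outcome. It also fixes centre as a stratification factor without using it. If the t or Mann-Whitney pair was meant for outcomes too, a normality check would choose the primary test, and no single effect estimate would be fixed.

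Three stronger readings are tempting, and the document does not support them.

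- **That repeated-measures ANCOVA is assigned to the egg count.** It is not; the sentence is limited to longitudinal data.
- **That omitting centre biases the result or inflates false positives.** It does the reverse: the test becomes conservative.
- **That the trial is short of power and is discarding strong predictors.** The article prints no SD for 11 versus 9 and refers to supplementary files that are not at hand. With an SD near 3.05, 49 per arm gives 90% power. The entry limits on AFC, AMH and age narrow their range, so their predictive strength in these women is unknown and may be modest.

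**Conclusion.** The point holds as one of specification and efficiency. As written, no efficacy analysis is assigned to the primary outcome, and neither the stratification factor nor the recorded baseline variables enter any stated analysis. The first part rests on the text alone. The size of the second rests on assumed variance shares. Leaving out centre costs almost nothing if centres are alike, and lowers the true type I error to about 4% or 3% if centre explains 10% or 20% of the variance. Baseline adjustment would cut the standard error by about 3% to 16% for R² of 5% to 30%, with the low end plausible under the entry criteria. The treatment estimate is not biased in either case. The change should be made, but the trial's validity does not depend on it.

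**What to change.** In Data analysis, name one primary analysis:

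- **Population:** the full analysis set, with women who have no eggs retrieved counted as zero. This needs saying because failure to obtain eggs is a discontinuation criterion.
- **Model:** a linear model for number of eggs with terms for treatment, centre, baseline AFC, AMH and age, and robust standard errors.
- **Estimate:** the adjusted mean difference with its 95% CI. This is the same quantity, a difference in means, on which the sample size was planned.

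Use the same model for the 2PN, cleavage, grade I embryo and follicle counts. Keep repeated-measures ANCOVA only for variables that are measured repeatedly, and name them.

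The cost is a few sentences and minimal programming. Centre, AFC, AMH and age are already recorded, so no new data are needed. The change should be dated before unblinding.

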### Estimation of the sample size

In a recent study in China, it was reported that in conventional IVF or ICSI, the total number of retrieved eggs in the treatment group (259.77±25.45) was significantly higher than that in the placebo group (235.59±26.44). In this study, the number of eggs obtained in the Guiluxian group was 11 under the original hypothesis and 9 under the alternative hypothesis (9 in the placebo group). The bilateral *Z* test of the combined variance will be used to estimate the sample size at 0.05 level of significance. The ratio between groups will be1:1. The minimum sample size found for each group is 49 people, hence a total of 98 people. Besides, 90% of the detection ability will be obtained, and the difference in ratio between groups is 0.15. Considering a dropout rate of 15%, we will be expected to enroll 120 participants, with 60 participants in each group (see supplementary files 1 and 2 for details).

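### Fisher's exact test is valid but conservative for per-woman pregnancy outcomes; Boschloo's exact test keeps the same error guarantee and adds about 5 points of power

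*Protocol article*

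**What the plan says.** The Data analysis section makes every test two-sided. For comparing ratios between the arms it names Fisher's test, in these words: "exact rate method with a significance level defined as a value < 0.05". It gives no rule based on expected counts, so Fisher's test covers every outcome ratio. For the baseline comparison the same section says that "frequencies will be compared using chi-square tests".

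The Outcome measurement section makes the number of eggs the primary outcome. Among the secondary outcomes it lists "persistent pregnancy rate", which can be read as one yes/no result per woman. Clinical pregnancy rate is named as a comparison in the abstract only. On size, the Estimation of the sample size section says "we will be expected to enroll 120 participants, with 60 participants in each group".

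**The concern.** Fisher's test conditions on the total number of events. In trials of this size its attainable p-values are coarse, so its true error rate lies well below the nominal level. A real difference in pregnancy is then harder to show than a 5% error rate requires.

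Pregnancy is closer than egg count to the stated aim, which is the effect on IVF-ET outcome. It is a secondary outcome for which the article makes no power claim. At 60 per arm power is modest under any test, so power that can be had without relaxing the error rate is worth having.

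The point is limited to outcomes with one yes/no result per randomised woman. Implantation rate is usually counted per embryo and abortion rate per pregnancy. Those have other denominators and are not addressed here.

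**Working it through.** **Inputs from the article.** Two-sided testing at 0.05 (Data analysis). Allocation: "The ratio between groups will be1:1". The stated minimum is 49 per group; with 15% dropout, 49 / 0.85 = 57.6, so 58, and 60 are planned. If 15% of 60 are lost, 60 × 0.85 = 51 remain per arm.

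**Assumptions.** No expected pregnancy rate is given. A difference in ratio of 0.15 appears in the sample-size section, but without a base rate and without being tied to pregnancy. I therefore take common rates of 5-50% for the error rate, and three illustrative pairs of rates for power. The denominator is all randomised women.

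**Plan's own figure.** The article states no power or true error rate for any ratio outcome, so there is nothing to reproduce beyond the 0.05 threshold.

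**Method.** With n per arm, list all (n + 1)² tables (61 × 61 at n = 60). Let R be the set of tables (a, b) that a test rejects. Then

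- size(p) = Σ over R of Bin(a; n, p) × Bin(b; n, p)
- power(p₀, p₁) = Σ over R of Bin(a; n, p₀) × Bin(b; n, p₁)

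R for Fisher is p < 0.05. R for chi-square is the uncorrected Pearson p < 0.05. R for Boschloo is Fisher's p at or below the largest cutoff that keeps the maximum of size(p) at or below 0.05. At n = 60 that cutoff is 0.0665. Because it exceeds 0.05, Boschloo's region contains Fisher's.

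**True size, 60 per arm**

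| Common rate | Fisher | Boschloo | Chi-square |
|---|---|---|---|
| 5% | 1.1% | 2.7% | 4.6% |
| 10% | 2.2% | 3.4% | 5.1% |
| 20% | 2.8% | 4.0% | 5.0% |
| 30% | 3.1% | 4.1% | 5.3% |
| Maximum over all rates | 3.5% | 4.9% | 5.5% |

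**Power, 60 per arm**

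| Rates | Fisher | Boschloo | Chi-square | Boschloo − Fisher | Chi-square − Fisher |
|---|---|---|---|---|---|
| 15% vs 30% | 41.8% | 47.3% | 51.4% | 5.5 | 9.6 |
| 10% vs 25% | 49.4% | 54.8% | 58.5% | 5.4 | 9.1 |
| 20% vs 40% | 60.0% | 64.6% | 68.4% | 4.6 | 8.4 |

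Over the wider set of scenarios at n = 60, the gain of Boschloo over Fisher is about 3-7 points.

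**At 51 per arm.** Fisher's size is 1.8-3.1% at rates of 10-30%. For 15% vs 30%, power is 36.4% (Fisher), 41.5% (Boschloo) and 44.8% (chi-square). The maximum size is 4.8% for Boschloo and 5.9% for chi-square. The gain over Fisher varies more with the rates here, from about 1 point (40% vs 55-65%) to nearly 8 (5% vs 15%).

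**The case against.** The strongest reply is that nothing here is wrong. The article gives 0.05 as a threshold, not as a claim about the achieved error rate, and a test whose size never exceeds 0.05 meets it. Fisher's test is conventional and holds at any rate and any arm size. That is an advantage in a population with poor ovarian response, where low pregnancy rates cannot be excluded. All of this stands.

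Three stronger readings are tempting, and the article does not support them.

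- A reader might infer that chi-square at baseline and Fisher for outcomes is a contradiction. The two tests serve different purposes, so it is not.
- A reader might infer that Fisher's test gives up 8-10 points of power for nothing. That gap is to uncorrected chi-square, whose size can exceed 5%. Fisher's guarantee is real, and part of the gap is its price.
- A reader might infer that chi-square should simply replace Fisher. That is a debatable trade: its excess over 5% reaches 0.5 points at 60 per arm and 0.9 at 51.

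It is also fair that the rates are assumed and that the denominator is not fixed. Women with no egg or no embryo meet the discontinuation criteria, so a per-transfer denominator is possible. The full analysis set of all randomised women supports the per-woman reading but does not settle it for this outcome.

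What the reply does not answer is the comparison with Boschloo's test. It gives the same guarantee, also works at low rates, and rejects every table that Fisher's test rejects, plus some more.

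**Conclusion.** The plan is valid on this point and can be improved at no cost in type I error. For per-woman yes/no outcomes at 60 per arm, Fisher's true size is 2.2-3.1% at assumed rates of 10-30% and never above 3.5%. Against an equally strict exact test it loses about 5 points of power (4.6 to 5.5 in the three scenarios shown). The exact loss depends on rates that the article does not give; that Boschloo's test is at least as powerful does not.

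The importance is minor. Only secondary outcomes are touched, the primary outcome is unaffected, and power for a 15-point difference stays near 50% even after the change.

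**What to change.** Before unblinding, add one sentence to the Data analysis section: yes/no outcomes with one result per woman (persistent pregnancy and, if it is kept as an outcome, clinical pregnancy) are counted over all randomised women and compared between arms with a two-sided Boschloo unconditional exact test at 0.05 instead of Fisher's test. The critical value is computed for the arm sizes actually analysed.

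The cost is that sentence and a less familiar test name; no patients, data or type I error are spent. The timing matters: choosing between tests after the allocation is known would be open to bias.

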### Data management

Specialized data management physicians in each reproductive center will collect information on the patient number and various data of the patients during the trial to ensure that the information will not be disclosed. All data collected will be saved for 5 years after publication. Electronic data will be stored in password-protected computers and access will only be allowed to the principal investigator. The data were uniformly managed by the database of the Reproductive Center of Shandong University of Traditional Chinese Medicine. Data obtained will only be restricted for use in this study.

### Supervision and management

We have also established a Data Monitoring Committee (DMC). The DMC is composed of the director of the Department of Reproductive Center of Shandong Provincial Hospital of Traditional Chinese Medicine as the chairman and the heads of the other two study sites as independent members. It is the responsibility of the DMC to monitor data, assess adverse events and cases of abnormal liver and kidney function results post-intervention on a regular monthly basis, review the core trial process, conduct interim analyses (the interim analysis includes the evaluation of the patient's follicular growth status, the number of retrieved oocytes and the incidence of adverse events. If the incidence of events of early follicular ovulation and absence of follicles after stimulation is as high as 30%, or the incidence of adverse events is as high as 10%, the trial will be terminated and the reasons for this will be analyzed.), and discuss relevant protocol amendments.

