### Trial status

The trial was registered at the Chinese Clinical Trial Registry (ChiCTR) which is assigned to be the representative registry of China to join WHO ICTRP in 2007.

This trial is at version 1.3, 16 December 2019 (ChiTR).

The actual study start date was 1 July 2020 and the anticipated study end date is 31 December 2021. The recruitment start date was 15 October 2020; the anticipated recruitment end date is 31 January 2022.

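### The mandatory 10% and 30% termination limits have no minimum number of women, stated arm or look timing, and the heads of study sites who apply them are called independent

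*Protocol article*

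**What the plan says.** The Protocol article, under Supervision and management, sets up a Data Monitoring Committee. It assesses adverse events and abnormal liver and kidney results "post-intervention on a regular monthly basis, review the core trial process, conduct interim analyses". The parenthesis after those words says what the interim analyses cover (follicular growth, retrieved oocytes, adverse events) and gives two limits. The first begins "If the incidence of events of early follicular ovulation and absence of follicles after stimulation is as high as 30" per cent. The second reads "or the incidence of adverse events is as high as 10%, the trial will be terminated".

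Neither limit comes with a denominator, an arm, a severity or relatedness qualifier, or a measure of precision.

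On membership, "The DMC is composed of the director of the Department of Reproductive Center" at a provincial hospital, as chair, with "the heads of the other two study sites as independent members". The reference to the other two sites implies that the chair's centre is also a study site.

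Under Randomization and blinding, "The clinicians and patients will be blinded to the drug allocation until the end of the study". Under Adverse events, the safety analysis covers only women who received Guilu Xian, so no comparison with placebo is stated there.

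**The concern.** The wording is mandatory: the trial is terminated once an observed proportion reaches the limit. A raw proportion on few women is very imprecise, and both event types are foreseen in this population. The Trial design section lists nausea, no dominant follicle and early ovulation among the reasons for individual discontinuation. Followed literally at small numbers, the rule could end the trial unanswered although the true rates are well below the limits.

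The open denominator matters in the other direction too. If the proportion is taken over both arms, an excess confined to one arm is halved by 1:1 pooling and may stay under the limit at a given look.

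The people who apply the rule head the sites being monitored, so calling them independent misdescribes the oversight.

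**Working it through.** The protocol states no error rate or operating characteristic for the rule, so there is no figure to reproduce. The calculations below show what the rule does under stated assumptions.

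**Inputs from the protocol**
- Limits: 10% for adverse events and 30% for early ovulation or absent follicles (Supervision and management).
- Sample: "we will be expected to enroll 120 participants, with 60 participants in each group" (Estimation of the sample size).
- Accrual: "The recruitment start date was 15 October 2020; the anticipated recruitment end date is 31 January 2022" (Trial status). This is about 15.5 months, and 120/15.5 = 7.7, so about 8 women a month.

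**Assumptions**
- Accrual is uniform, and looks are cumulative and pooled.
- The true event rates are not given in the protocol and are shown as ranges.
- In the monthly reading, looks fall at n = 8, 16, ..., 120 (15 looks).

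**Method**
- At each look the rule is met if events/n ≥ limit.
- The chance of ever meeting it comes from an exact binomial recursion. The distribution of cumulative events is carried from look to look, and the probability at or above the limit is removed and summed.

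**First look.** One event in 8 is 1/8 = 12.5%, which is at or above 10%, with an exact 95% interval of 0.3% to 52.7%. The chance of at least one event is 1 − (1 − p)^8. At p = 2% this is 1 − 0.98^8 = 14.9%, and at p = 5% it is 1 − 0.95^8 = 33.7%.

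**Chance of ever meeting the 10% limit**

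| True rate | Looks every 8 women | Looks at 60 and 120 | Every 8, none before 40 |
|---|---|---|---|
| 2% | 16% | 0.1% | 0.9% |
| 5% | 43% | 8% | 17% |
| 7% | 62% | 28% | 41% |

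With 4 to 10 women per look, the first column ranges over 14–20% at a true 2% and 42–50% at a true 5%.

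**Chance of ever meeting the 30% limit, looks every 8 women.** This is 15%, 33% and 59% at true rates of 15%, 20% and 25%. With a single look at 60 women it is 4% at a true 20%.

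**Excess in one arm, pooled reading**
- 11/60 = 18.3% against 0/60 (Fisher p = 0.0006) pools to 11/120 = 9.2%. That is below 10%, so the rule is not met at that look.
- Over all looks every 8 women, true rates of 15% and 0% meet the pooled rule in 67% of trials, and 18% and 0% in about 80%.
- At a single look at 120 women, 15% and 0% meet it in 18%.

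**The case against.** The strongest reply is that the large figures depend on readings the text does not settle.

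- **Timing.** The monthly frequency is attached to the review of adverse events and laboratory results, while the limits sit with the interim analyses, which have no stated timing. A reader might infer a monthly termination rule, but the protocol does not say so. This stands, and it is why the two-look figures are shown beside the monthly ones.
- **Pooling.** The text does not say that incidence is pooled. This also stands. The one-arm example holds only under the pooled reading.
- **The two risks pull against each other.** Frequent early looks raise the chance of a false stop but also make a one-arm excess likely to trigger the rule. Few looks do the reverse. This stands: the two worst cases should not be added together.
- **Condensed article.** Denominators and look timing often sit in a full protocol or committee charter. That would excuse silence. Here, though, a binding rule is stated in terms that cannot be applied without those details, and the label of independence is stated outright.

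A reader might also infer that the committee's view of oocyte numbers, the primary outcome, biases the trial. The protocol does not say that counts are seen by arm, keeps clinicians blinded, and has no efficacy stopping rule. No such bias is shown.

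**Conclusion.** The concern holds as a badly fixed stated rule. Termination is mandatory at raw proportions with no minimum number, no stated arm or pooling and no stated look timing, and heads of study sites are described as independent.

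The size of the false-stop risk depends mainly on the number of looks. At an assumed true adverse-event rate of 5%, the chance of meeting the 10% limit is 43% with looks every 8 women and 8% with looks at 60 and 120. At 2% it is 16% or 0.1%. These figures rest on uniform accrual, pooled counts and assumed true rates.

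It would go too far to say that the rule will miss harm in one arm. It can do so at a given look if incidence is pooled, but repeated early looks would often trigger it.

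**What to change.** Keep the sponsor's 10% and 30% figures and amend the Supervision and management section as follows.

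1. State when the interim looks take place, and a minimum cumulative number of treated women before the automatic limits bind. Individual adverse-event review continues from the first woman. As an illustration, with no binding look before 40 women, the chance of meeting the 10% limit at a true 2% or 5% falls from 16% or 43% to 0.9% or 17%. The number itself is the sponsor's to choose.
2. State the denominator. Show incidence by coded arm beside the pooled figure, in tables prepared by the holder of the randomisation list.
3. Delete the word independent for members who head a study site.

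The cost is protocol wording and one coded table per look. The downside is that an automatic stop cannot occur in the first few months: at about 8 women a month, 40 women take 40/8 = 5 months.

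A trigger based on a lower confidence bound is not recommended as the replacement. With an exact one-sided 95% bound applied per arm, it needs 11 of 60 women in that arm to have an event before the 10% figure acts. With looks every 4 women in the arm, it detects a true rate of 18% only 67% of the time.
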